#### Secondary outcome analysis

We will use Program Cost Analysis [23] to quantify total program costs, total costs per clinic, and total costs per member per month (PMPM) for the non-intervention and intervention periods. We will work with KPD and PDA staff to develop realistic real-world estimates of the staff time and resources used to develop and print a workbook, including staff time that would be needed to conduct an appropriate literature review, collect and assess health records data, develop clinic monitoring processes, and prepare, print, and distribute a completed workbook. Staff time for meetings, workbook review, the deliberative forum, post-forum survey, and relevant clinic follow-up meetings will be documented, and average labor costs, by profession type, will be assigned. Costs for selected implementation strategies (equipment, trainings, CE, staff time) will be obtained from clinic managers and other KPD and PDA staff during the implementation period. Treatment costs (procedure costs based on local market paid claims) for eligible tooth surfaces and patient-paid costs will be obtained from the electronic health records. All costs will be reported in 2021 dollars.

An incremental cost-effectiveness ratio (ICER) will be estimated using the following formula: (mTCi − mTCc) / ( mSPRi − mSPRc), where mTCi and mTCc represent the mean total intervention costs for clinics during the non-intervention and intervention periods, including NCCL treatment costs, and mSPRi and mSPRc represent the mean cumulative sealant placement rates for eligible teeth among patients with a routine care visit over the 12-month evaluation period for each clinic. We will calculate ICERs and bootstrapped confidence intervals methods based on the data [24]. We expect differences in both costs and sealant placement rates to be unequivocally positive. If, however, the results are equivocal, we will conduct simulation modeling using bootstrapping and incremental net benefit approaches to assess the effects of model input variability on outcomes [25–27]. Incremental net benefit analysis allows adjustment for known statistical issues associated with confidence intervals (CIs) for equivocal ICERs by estimating CIs around the organizations (payer’s) willingness to pay for the intervention.

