## Abbreviations

ADA: American Dental Association
CEA: Cost-effectiveness analysis
CI: Confidence interval
DISGO: Dissemination and Implementation of Sealant Guidelines in Organizations
E1/E2: Enamel lesions
EHR: Electronic health record
ICER: Incremental cost-effectiveness ratio
KPD: Kaiser Permanente Dental
mSPRi: Mean cumulative sealant placement rates for eligible teeth among patients with a routine care visit at clinics following the intervention
mSPRc: Mean cumulative sealant placement rates for eligible teeth among patients with a routine care visit at clinics before the intervention
mTCi: Mean total intervention costs at clinics following the intervention
mTCc: Mean total intervention costs at clinics before the intervention
NCCL: Non-cavitated carious lesion
PDA: Permanente Dental Associates
PMPM: Per member per month
UBT: Unit-Based Team

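### The ICER definition in the Methods conflicts with the abbreviation list, and its formula differences raw cost totals and before-after rates without regard to period length or calendar time

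*Protocol article*

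**What the plan says.** The protocol article, Secondary outcome analysis, prints the estimator in full: "An incremental cost-effectiveness ratio (ICER) will be estimated using the following formula: (mTCi − mTCc) / ( mSPRi − mSPRc"). It defines the cost terms with "where mTCi and mTCc represent the mean total intervention costs for clinics during the non-intervention and intervention periods", and adds that NCCL treatment costs are included. It defines the two effect terms jointly, as "mean cumulative sealant placement rates for eligible teeth among patients with a routine care visit over the 12-month evaluation period for each clinic".

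The Abbreviations section defines the same terms in the other direction and one by one:
- The cost term with subscript i is given as "mTCi: Mean total intervention costs at clinics following the intervention".
- Its counterpart with subscript c is given as "mTCc: Mean total intervention costs at clinics before the intervention".
- The placement rate with subscript i is given as "mSPRi: Mean cumulative sealant placement rates for eligible teeth among patients with a routine care visit at clinics following the intervention".
- The placement rate with subscript c has its own entry, which reads "mSPRc: Mean cumulative sealant placement rates for eligible teeth among patients with a routine care visit at clinics before the intervention".

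The section on cost and cost-effectiveness under Measures describes the contrast as intervention period against usual care in the control period. It also plans PMPM costs for each period. The Secondary outcome analysis section expects the cost difference and the rate difference both to be positive. Allowance for secular trend, where needed, appears only under Primary outcome analysis.

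**The concern.** Cost-effectiveness is the named secondary outcome. Under Acceptability, its results are to be shown to management, who then rate the acceptability and feasibility of the process, so a faulty ICER would feed another study measure.

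Three features of the printed definition are troublesome:
- **Labels and periods.** The Methods text and the abbreviation list disagree on which period each cost term belongs to. The Methods text gives no separate period for either placement rate.
- **Totals.** Treatment costs accumulate with time. In a stepped wedge, clinics spend very different lengths of time in each condition, so a difference of totals partly measures months observed.
- **Calendar time.** Control months come early in 2021 and intervention months late. A plain difference of period means takes up whatever changed over the year, which the staggered design would allow an analyst to separate.

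**Working it through.** **1. Labels, side by side**

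| Term | Secondary outcome analysis, read in order | Abbreviations |
|---|---|---|
| mTCi | non-intervention | following the intervention |
| mTCc | intervention | before the intervention |
| mSPRi | joint 12-month definition | following the intervention |
| mSPRc | joint 12-month definition | before the intervention |

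Illustration of the sign: take an assumed cost difference of 1 unit and the rate difference from the Power section, 10% − 3% = 0.07. The intended ratio is 1/0.07 = +14.3. The Methods labels, applied literally to costs only, give −1/0.07 = −14.3.

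**2. The plan's own period lengths**

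Study design and recruitment states 98 non-intervention and 101 intervention clinic-months. Adding the monthly rows of Table 1 reproduces both, although the table's printed totals are 114 and 117. However, 16 clinics over 12 months give 192 clinic-months, not 98 + 101 = 199, and the June to September rows add to 17, 18, 19 and 17 clinics. The start counts add to 16, so I rebuilt from them:

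| Start | Clinics | Control months | Intervention months | Difference |
|---|---|---|---|---|
| Mar | 1 | 2 | 10 | +8 |
| Apr | 1 | 3 | 9 | +6 |
| May | 2 | 4 | 8 | +4 |
| June | 3 | 5 | 7 | +2 |
| July | 1 | 6 | 6 | 0 |
| Aug | 2 | 7 | 5 | −2 |
| Sept | 4 | 8 | 4 | −4 |
| Oct | 2 | 9 | 3 | −6 |

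This gives 98 control and 94 intervention months (192 in all), or 6.125 and 5.875 per clinic.

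**3. Effect of differencing totals**

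Let C be the monthly NCCL treatment cost per clinic, the same in all clinics and unaffected by the intervention, and P the programme cost per clinic. Both are assumptions, since the article gives no costs.

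- Mean month difference: (8 + 6 + 2×4 + 3×2 + 0 − 2×2 − 4×4 − 2×6)/16 = −4/16 = −0.25.
- Sum of squares: 64 + 36 + 32 + 12 + 0 + 8 + 64 + 72 = 288. SD = √[(288 − 16×0.25²)/15] = √19.13 = 4.37. Standard error = 4.37/√16 = 1.09.
- Mean cost difference: P − 0.25C. At P = 0.25C this is 0, at P = 1C it is 0.75C, and at P = 2C it is 1.75C.
- With the stated 101 months: (101 − 98)/16 = +0.19, so the shift would be +0.19C.
- If whole clinics are resampled, the spread in months alone contributes a standard error of about 1.1C to the cost difference.

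**4. Calendar time**

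A clinic with k control months has mean calendar month (k + 1)/2 before and (k + 13)/2 after. The gap is (k + 13)/2 − (k + 1)/2 = 6 for every k. A linear drift of b per month in the placement rate, with steady monthly volume, therefore adds 6b to a clinic's rate difference. A drift in monthly cost does the same to a per-month cost difference. Pooled over clinic-months, the means are month 3.9 (control) and 9.2 (intervention). For scale, a drift of 7/6 = 1.17 percentage points a month would by itself produce the whole 7-point difference assumed in the Power section.

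**The case against.** The case for leaving this as a small clarification is strong in parts.

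- **The document resolves the labels.** Abbreviations, the Measures section and the expectation of positive differences all point the same way. A reader might infer that the trial will report an ICER of the wrong sign. An analyst who reads those places would not compute one. This stands: it is a drafting error in the operative paragraph.
- **The rates need not share a window.** A reader might infer that both rates are computed over the same 12 months, leaving the denominator undefined. The 12-month phrase may instead describe the routine care visit or the overall data window, and Abbreviations separates before from after. This stands: it is an ambiguity to reconcile.
- **The length bias nearly cancels.** The +8C and −6C figures are single-clinic extremes, and the formula averages over clinics. This stands for the mean. It does not remove the added noise, and the near-cancellation relies on equal C, whereas clinics were chosen as small, medium and large.
- **PMPM costs by period are already planned.** True, but the ICER formula does not use them.
- **Estimation detail may lie in a fuller document.** That would answer a point about silence. Here the article prints the estimator as a difference of period means of total costs, so the point concerns what is stated.

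Reporting net benefit in every case and the choice of bootstrap unit are matters of preference, and I do not press them.

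**Conclusion.** The point holds as an inconsistency and a poorly chosen basis for a secondary outcome. It leaves the primary analysis untouched.

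The Methods paragraph contradicts the abbreviation list on the cost terms and does not give each placement rate its own period. On any reading, those two passages must be reconciled.

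The totals basis produces little bias in the mean: about −0.25C with 94 intervention months, or +0.19C if the stated 101 is used. Its larger effect is noise, with an artefactual standard error of about 1.1C in a whole-clinic bootstrap. At P = 1C that exceeds the programme cost itself, and at P = 2C it is roughly half of it. These figures assume one constant C across clinics and no effect on treatment cost.

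The 6-month separation is exact for every clinic, and it matters most if practice or costs drifted during 2021. The article does not allow the size of a trend, or of C relative to P, to be judged. It therefore does not support a claim that the ICER will be materially wrong, only that the printed estimator does not protect against it.

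**What to change.** In Secondary outcome analysis:
1. Define i as intervention and c as non-intervention for all four terms, matching Abbreviations.
2. State the period over which each placement rate is computed, and what the 12-month phrase refers to.
3. Put ICER costs on a per-clinic-month basis or on the PMPM basis already planned. Add one-off costs of the deliberative loop separately, because dividing a fixed cost by 3 to 10 months would bring period length back in.
4. Estimate both increments, cost and placement rate, with adjustment for calendar time.

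Reconcile the intervention column and printed totals of Table 1 with the start counts before using them as denominators.

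The price is a rewritten paragraph and modest extra analysis work. The cost items and health-record data needed are already in the collection plan.

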#### Exploratory analysis of putative mediators

We will examine whether having an informed opinion and perceptions of voice mediate the relationship between exposure to the intervention and the use of sealants on NCCL. We will use causal inference methods [28] that have been extended to allow for multiple mediators, as well as exposure-mediator and mediator-mediator interactions. This framework includes both regression-based approaches and approaches based on inverse probability weighting. We will default to the regression-based approach. If model fitting issues are present, we will use the inverse probability weighting approach.

#### Additional analyses

We will use descriptive analyses to characterize adoption, fidelity, and acceptability. In addition, we will use descriptive statistics to characterize clinics’ selection and deployment of implementation strategies.

## Discussion

The purpose of this study is to examine whether introducing the deliberative loop process to an organization enables the clinics within the organization to identify implementation strategies for the organization’s pit-and-fissure dental sealant guideline. The deliberative loop process is a decision-making process that draws on the lived experience of stakeholders and engages difference as a resource. This study will determine whether the deliberative loop process assists clinic leadership at an organization that values and practices shared decision-making in selecting implementation strategies that improve provider adherence to a guideline. There is little information about effective implementation processes for large group dental practices. Our study may be the first to introduce a process that includes both top-down and bottom-up elements. The top-down element supports clinic leadership in their decision-making powers. The bottom-up element elicits the desirability to providers and staff of a range of clinic-level implementation interventions and provides this information to clinic leadership.

Strengths of the study include being guided by theory, having an intervention that addresses identified barriers, and receiving strong support from KPD leadership. With this support, we were able to randomize clinics to steps and optimize the intervention to the needs of the clinics. There are limitations that must be considered, as well. The intervention comprises three components. Because all clinics are receiving all components, should the intervention be successful, we will not have information about the components that contribute to that success. Additionally, because we are conducting this study in the context of one organization with its culture of shared decision-making, should the intervention be successful, we will not be able to determine the cultural parameters that contribute to that success. Finally, the measures characterizing perceptions of voice during the deliberative forum and UBT meetings are both taken following the deliberative forum. Although the retrospective measure of voice during UBT meetings could lack validity and thus bias the results, we believe that the measure could be more valid because the stakeholders have an alternative, the deliberative forum, to use as a comparison. This study will not be able to assess this possibility, however.

## Conclusion

One aspect of an implementation process involves selecting the implementation strategy to deploy. This study seeks to evaluate the effectiveness of the deliberative loop process, in which leaders select implementation strategies (i.e., top down) informed by the opinions of those who will be affected by the policy (i.e., bottom up), to increase provider adherence to the pit-and-fissure dental sealant guideline. The results of this study will be of interest to any organization considering how best to select implementation strategies to deploy and to the field of implementation science as a whole.

## Data Availability

Data sharing is not applicable to this article as no datasets were generated or analyzed during the current study.

## Abbreviations

ADA: American Dental Association
CEA: Cost-effectiveness analysis
CI: Confidence interval
DISGO: Dissemination and Implementation of Sealant Guidelines in Organizations
E1/E2: Enamel lesions
EHR: Electronic health record
ICER: Incremental cost-effectiveness ratio
KPD: Kaiser Permanente Dental
mSPRi: Mean cumulative sealant placement rates for eligible teeth among patients with a routine care visit at clinics following the intervention
mSPRc: Mean cumulative sealant placement rates for eligible teeth among patients with a routine care visit at clinics before the intervention
mTCi: Mean total intervention costs at clinics following the intervention
mTCc: Mean total intervention costs at clinics before the intervention
NCCL: Non-cavitated carious lesion
PDA: Permanente Dental Associates
PMPM: Per member per month
UBT: Unit-Based Team
